## Abstract

**Background:**

This study protocol adapts the traditional homeopathic drug proving methodology to a modern clinical trial design.

**Method:**

Multi-centre, randomised, double-blind, placebo-controlled phase 1 trial with 30 healthy volunteers. The study consists of a seven day run-in period, a five day intervention period and a 16 day post-intervention observation period. Subjects, investigators and the statisticians are blinded from the allocation to the study arm and from the identity of the homeopathic drug. The intervention is a highly diluted homeopathic drug (potency C12 = 10^24^), Dose: 5 globules taken 5 times per day over a maximum period of 5 days. The placebo consists of an optically identical carrier substance (sucrose globules). Subjects document the symptoms they experience in a semi-structured online diary. The primary outcome parameter is the number of specific symptoms that characterise the intervention compared to the placebo after a period of three weeks. Secondary outcome parameters are qualitative differences in profiles of characteristic and proving symptoms and the total number of all proving symptoms. The number of symptoms will be quantitatively analysed on an intention-to-treat basis using ANCOVA with the subject's expectation and baseline values as covariates. Content analysis according to Mayring is adapted to suit the homeopathic qualitative analysis procedure.

**Discussion:**

Homeopathic drug proving trials using the terminology of clinical trials according GCP and fulfilling current requirements for research under the current drug regulations is feasible. However, within the current regulations, homeopathic drug proving trials are classified as phase 1 trials, although their aim is not to explore the safety and pharmacological dynamics of the drug, but rather to find clinical indications according to the theory of homeopathy. To avoid bias, it is necessary that neither the subjects nor the investigators know the identity of the drug. This requires a modification to the informed consent process and blinded study materials. Because it is impossible to distinguish between adverse events and proving symptoms, both must be documented together.

**Trial registration:**

ClinicalTrials.gov identifier: NCT01061229.

## Background

Homoeopathic drug proving trials (HDP), also known as homeopathic pathogenetic trials, is one of the fundamental concepts of homeopathy and has been conducted for more than 200 years [1-4]. In addition to exposing the toxic effects of the drug, HDP serve as a key source of information for the homeopathic *materia medica*. Its purpose is to test non-toxic levels of a specific substance in healthy volunteers to determine the symptoms this substance stimulates and the types of individuals who may be sensitive to it. The profile of symptoms, recorded in an HDP by a group of healthy volunteers, serve as basis for information to find indicators of the drug in sick patients. In HDP, the drug under investigation is administered and the individual response of every volunteer to the application of the substance is described. According to the law of similars, the substance is then used to treat patients with similar symptoms. The clinical experience subsequently shapes the homeopathic drug profile.

A systematic review published in 2007 analysed HDP conducted between 1945 and 1995, showed that most HDP were of low methodological quality [1]. Most of these old HDP studies were conducted by homeopathic physicians who were mainly interested in identifying clinical indications and drug profiles for therapeutic purposes following the theory and philosophy of homeopathy. However, in recent years innovative new study methodology for HDP has been developed and tested [5-10].

Recent research [11] has focussed on two main objectives 1) using rigorous experimental designs to find out if specific effects of highly diluted homeopathic drugs compared to placebo or other controls can be identified or reproduced and 2) qualitatively identifying new symptoms and indications mainly for therapeutic purposes.

Current research in HDP focuses on re-proving old and commonly used homeopathic remedies in double-blinded and placebo-controlled trials. In these studies blinded homeopaths were asked to identify drug-specific symptoms in the diary of each study-subject and assign them to a list of potential homeopathic drugs. In the last blinded HDP conducted by this study group, two well-known homeopathic remedies (Natrium muriaticum and Arsenicum album) were tested against placebo. The blinded homeopaths identified only Arsenicum album-specific symptoms in the Arsenicum album group, only Natrium muriatricum specific symptoms in the Natrium muriaticum group and only non-specific symptoms in the placebo group. The results of this and a previous HDP showed that specific symptoms of the HDP could be identified and allocated by blinded raters with a high statistical significance [8,9,11]. To our knowledge, it is not clear whether the identification of drug-specific symptoms may also be achieved for new and unknown homeopathic drugs. Therefore, in our opinion, a key question of current HDP research is to define specific symptoms, including a list of criteria, and to develop a qualitative analysis method in order to identify them in new and unknown homeopathic drugs.

Homeopaths and researchers have developed a variety of study protocols for HDP and incorporated a variety of modern standards in the last few years [2,3,12-16].

National and European authorities require that the Guidelines for Good Clinical Practice (ICH GCP), the Declaration of Helsinki and the national drug regulations be applied for HDP and methodological and legal consequences must be considered. The European Committee for Homoeopathy (ECH) developed the "Homoeopathic drug proving guideline" [2] which for the first time, adapts traditional HDP methodology to the requirements of modern European standards. German drug regulations have meanwhile classified HDP as clinical phase 1 trials. Within this study we developed, for the first time, a study design methodology and a study-protocol that fulfils the criteria of a phase-1-trial, GCP, Declaration of Helsinki and German drug regulations and also tests its applicability and feasibility in practice. The main aim of the study is to determine whether a homeopathic drug in the potency C12 provokes more characteristic homeopathic proving symptoms after three weeks compared to a placebo in healthy volunteers. Therefore our hypotheses to test are:

H_0_: There is no difference between the number of characteristic symptoms provoked by a homeopathic drug in the potency C12 compared to placebo.

H_1_: There is a difference between the number of characteristic symptoms provoked by a homeopathic drug in the potency C12 compared to placebo.

Secondary aims are to develop and to test a qualitative analysis methodology on which to base a definition for drug-specific (characteristic) symptoms and to compile a profile of characteristic homeopathic proving symptoms of the drug being trialled for therapeutic purposes.

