### Intervention

Subjects in the intervention group are instructed to take five globules of the trial drug (potency C12), five times per day for a maximum of five days (5×5×5). The study medication is obtained from DHU (Germany), produced according to the Hahnemannian method [17]. Subjects are asked to stop taking the medication, in agreement with their investigator, if they experience any of a predefined set of proving symptoms (for definition see Table 1). Placebo consists of pure sucrose globules (DHU, Germany) that are not potentiated nor impregnated with alcohol. The administration scheme is identical in the placebo control group to that of the intervention group.

**Table 1 T1:** Criteria for proving symptoms and characteristic symptoms

Criteria for proving symptoms	Criteria for characteristic symptoms
New symptoms: the symptom is unfamiliar and has not been observed within the last year or during the run-in-period	Characteristic symptoms are defined as proving symptoms with a strongly individualistic character:

Study participant or study physician classify the symptom as new or unusual	Symptoms affecting the whole organism of one or more study participant

The study physician classifies the symptom as new in his final evaluation	Symptoms affecting different organs or organ systems of one or more study participant

A strong aggravation or modification of present (familiar) symptoms	Symptoms accompanying a variety of other symptoms

Present familiar symptoms that have disappeared during the proving (cure)	Symptoms that occur during the trial, which appear strange, peculiar or unique to one or more study participants

	Familiar symptoms from the past or present that have been cured or strongly alleviated

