### Sample size calculation

It is planned to include 30 healthy volunteers. Assuming a drop out rate of 20%, 24 subjects will be available for analysis. In this study, an unpaired t-test with a two-sided level of 5% has a power of 80% to detect a group difference of 20 ± 4 vs 15 ± 4 (mean ± standard deviation) characteristic proving symptoms.

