**Figure 3 F3:**
[figure not shown]
**Data analysis process in homeopathic drug proving trial**.

After closing the trial, the investigators obtain the complete body of text from the trial diary for each of their subjects and are asked to categorise "proving symptoms" in accordance to the prescribed definitions. Subsequently, a second investigator reviews coding and categorisation. In cases of contradictory categorisations, a review committee of two investigators will decide on the categorisation. At the end of this process, a list of proving symptoms for each subject will be compiled.

The categorisation of characteristic symptoms is the next step. To identify characteristic symptoms which occurred in more than one subject, an inter-subject comparison of each study arm is needed. However, investigators will still be blinded from the treatment allocation. This analysis is performed independently by two experienced investigators. The inter-coder reliability is calculated by the study statistician. The data is further structured into the following categories: localities, sensations, modalities and concomitants, times, mind and clinical findings.

Profiles of characteristic symptoms are compiled for both groups which can now be compared qualitatively.

Context analysis is the final part and will be conducted when the drug identity has been revealed at the end of the trial. The results will be related to the traditional and scientific knowledge available on the drug being investigated and discussed in the research team. The aim is to find out whether the data fits into the body of knowledge already available on the particular drug and its plausibility.

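### The plan treats characteristic symptoms as drug-specific, but Table 1 sets no condition against placebo, and the sample size assumes many such symptoms in both arms

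*Protocol article*

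**What the plan says.** The secondary aims (Protocol article, Background, after the hypotheses) concern a qualitative method and its product. They read, in part: "base a definition for drug-specific (characteristic) symptoms and to compile a profile of characteristic homeopathic proving symptoms of the drug being trialled for therapeutic purposes". The bracket equates the two terms. The Abstract does much the same when it calls the primary outcome a count of specific symptoms.

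Table 1 (section Intervention) supplies the working definition: "Characteristic symptoms are defined as proving symptoms with a strongly individualistic character". Of the five criteria beneath it, three are met by a single subject, for example "Symptoms affecting the whole organism of one or more study participant" and "Symptoms that occur during the trial, which appear strange, peculiar or unique to one or more study participants". None mentions placebo or the other arm. These definitions also serve as the predefined coding categories (Qualitative analysis) and define the primary outcome (Outcome parameters).

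The Sample size calculation gives 80% power "to detect a group difference of 20 ± 4 vs 15 ± 4 (mean ± standard deviation) characteristic proving symptoms".

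In the text after Figure 3, characteristic symptoms are compared between subjects within each arm, with coders blinded to allocation. Then: "Profiles of characteristic symptoms are compiled for both groups which can now be compared qualitatively". A context analysis against existing knowledge of the drug follows once its identity is known.

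**The concern.** A symptom can be called drug-specific only if it occurs more often with the drug than without it. Table 1 asks something else: whether the symptom is peculiar, general or accompanied by others in at least one person. A healthy volunteer on placebo can meet that, and the planning figures assume that volunteers in both arms will, many times each. The label therefore cannot carry the meaning that the secondary aim gives it.

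The profile is meant for therapeutic use, and the Background explains that such profiles guide the choice of drug for patients. The primary ANCOVA tests whether the mean count differs between arms. Even a positive result would not show which symptoms the drug caused, yet a profile labelled as the drug's own would be read that way. The randomised placebo arm holds the information needed to prevent this, and the described analysis makes no structured use of it at the level of single symptoms.

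**Working it through.** **Inputs.** From the Sample size calculation: 30 randomised, 20% dropout, 24 analysed, means 20 and 15, SD 4, unpaired t-test, two-sided 5%, power 80%. The allocation ratio is not stated in the text; 1:1 is assumed, giving 12 per arm.

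**The plan's own figure.** 30 × 0.8 = 24. Noncentral-t power for a difference of 5 with SD 4 is 79.6% at 11 per arm and 83.3% at 12 per arm. The smallest 1:1 total that reaches 80% is therefore 24, as stated. The figures 20 and 15 are thus the ones that the design rests on.

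**Share of reports.** Assume that 15 is the placebo mean and that the same background applies under drug. Then:

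- Share of drug-arm reports expected without the drug: 15/20 = 75%.
- At 12 per arm: 12 × 15 = 180 of 12 × 20 = 240 reports.
- At 15 per arm: 225 of 300.
- If the null hypothesis is true: 100%.
- Sampling error at 12 per arm (standard error of each mean 4/√12 = 1.15): the observed ratio of means would run from about 62% to 90% (simulated 95% range).

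**Share of distinct entries.** A profile lists different symptoms, not reports, and repeated reports collapse into one entry. Suppose that background reports are drawn at random from K possible symptoms and drug-related reports from M others, with n subjects. The expected number of distinct entries is K[1 − (1 − 1/K)^(15n)] for background and M[1 − (1 − 1/M)^(5n)] for drug.

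| n | K | M | Background share of entries |
|---|---|---|---|
| 15 | 50 | 1000 | 0.41 |
| 12 | 50 | 20 | 0.72 |
| 12 | 200 | 60 | 0.76 |
| 15 | 1000 | 5 | 0.98 |

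Across K from 50 to 1000 and M from 5 to 1000, the share runs from about 41% to 98%. K and M are assumptions, and nothing in the article fixes them.

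**What one symptom can show.** For k of 12 on drug and 0 of 12 on placebo, the two-sided Fisher p is 2 × C(12,k)/C(24,k):

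| k | p |
|---|---|
| 1 | 2 × 12/24 = 1.00 |
| 2 | 2 × 66/276 = 0.48 |
| 3 | 2 × 220/2024 = 0.22 |
| 4 | 2 × 495/10626 = 0.093 |
| 5 | 2 × 792/42504 = 0.037 |

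A symptom in one subject carries no evidence of attribution. At least 5 against 0 is needed for p < 0.05, before any allowance for the number of symptoms examined.

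**Steps that might separate drug from placebo.** The first proving-symptom criterion in Table 1 excludes symptoms seen in the past year or the run-in. It works within each subject and equally in both arms, so it lowers background without distinguishing the arms. The within-arm comparison finds repeated symptoms, not excess over placebo. The profile comparison comes after the profiles are compiled and has no stated rule. The context analysis asks about fit with prior knowledge, which is not a placebo comparison.

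**The case against.** Much can be said for the plan.

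- **Blinded coding.** Table 1 is applied in both arms under blinding. A criterion such as absence on placebo would break the blind and make the primary comparison circular. This stands: Table 1 need not change, and comparison with placebo belongs after coding.
- **A definition still under development.** The aim is to develop and test a method, and the Discussion admits that its suitability is unclear. This softens the equation of terms. It does not remove it, because Table 1 is already fixed for coding and for the primary outcome.
- **Other filters.** The novelty criterion and the planned profile comparison are both real, so it would be wrong to say that the plan has no safeguard or only one. Neither, as described, decides which symptoms may be attributed to the drug.
- **A condensed article.** The full protocol may say how the profile comparison works. That is a reason not to claim that no rule exists anywhere. The conflict between the stated aim, Table 1 and the planning means lies in the printed text.

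A reader might infer that 75% of the therapeutic profile would be background, or that the trial would publish mostly background symptoms as indications. The documents do not support either. The sample size section does not name the arms and the alternative is two-sided; reading 15 as placebo follows from the main aim, which speaks of more symptoms on drug. Equal background is not stated. The ratio concerns reports, not distinct entries. The article also does not say that every symptom reported once on drug will stand in the final profile.

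**Conclusion.** The point holds as a mismatch between aim, definition and planning figures. Characteristic, as Table 1 defines it, does not mean drug-specific, and the plan's own means have subjects in both arms averaging at least 15 characteristic symptoms. On the assumptions that 15 is the placebo mean and background is equal, about three quarters of drug-arm reports would be expected on placebo too. The share of distinct profile entries is unknown.

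The consequence is confined to the secondary qualitative aim. The primary test, its estimate and its error rate are untouched. It is still worth correcting, because the profile is intended for therapeutic use and the data needed to qualify it will already be in hand.

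**What to change.** 1. In the secondary aims, remove the equation of drug-specific with characteristic. Use characteristic for the Table 1 definition only, and align the Abstract's wording of the primary outcome.
2. In the qualitative analysis, build one symptom list across all subjects, coded before unblinding. After unblinding, publish for each symptom the number of subjects reporting it on drug and on placebo.
3. Describe the drug profile as exploratory. State that symptoms seen in a single subject, or about equally often in both arms, are not attributable to the drug.
4. Do not treat a higher count on drug than on placebo as proof of specificity. A split of 2/12 against 0/12 (p = 0.48) is well within chance. The Fisher values above show how little one symptom can prove; they are not a proposed test.

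The cost is a shared code list across arms and one table from data that are coded anyway. No extra subjects or data are needed, and the primary analysis does not change. The downside is a shorter and more modest drug profile.

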## Methods

### Study design

The homeopathic drug proving trial is to be conducted as a multi-centre, randomised, double-blind, placebo-controlled phase 1 trial. Subjects and investigators are not only blinded to the group allocation process but also to the identity of the drug.

### Subjects

Volunteer medical students or medical doctors are invited to take part in the trial by their investigators via email or phone.

Subjects can be included if they fulfil the following criteria: Medical doctors or medical students, over 18 years of age, who are not being treated for any acute or chronic diseases on the day of inclusion, plus written informed consent.

The following exclusion criteria apply: pregnant women or nursing mothers are excluded as are anyone who have received homeopathic treatment over the previous six weeks, or anyone who has participated in another clinical trial during the last six months, anyone with a personal or professional dependence on the study physician or sponsor as well as anyone who has been placed in hospital or other institution by authorities or decree.

### Investigators

The investigators are homeopathic medical doctors with knowledge of HDP and who have at least three years practical experience in homeopathic therapy. All investigators are required to have completed a two-day certified and standardised investigator training programme based on GCP, Declaration of Helsinki and the national drug regulations as well as specific training in the study procedures of this trial.

### Ethics and consent

All subjects will provide written informed consent prior to the inclusion in the trial. The trial will be performed in accordance with International Conference on Harmonisation Guidelines for Good Clinical Practice (ICH GCP), Helsinki Declaration and national drug regulations. Information about the trial will be provided during one-on-one interviews with the help of a written brochure for subjects. The study was approved by the Berlin Ethics Committee (Landesamt für Gesundheit und Soziales Berlin) on the 17th August 2009 (Reference: ZS EK 15, 287/09). The trial was registered under ClinicalTrials.gov: Identifier NCT01061229.

### Procedures

The study consists of a seven day run-in period (baseline observation), a five day intervention period followed by a 16 day follow-up period (see Figure 1).

**Figure 1 F1:**
[figure not shown]
**Organisation process in homeopathic drug proving**.

Each study centre consists of one investigator who supervises a maximum of three subjects. After giving informed consent, subjects will receive an initial physical examination, a full-length homeopathic interview of 60-120 minutes duration and training on formal and technical aspects of documentation prior to the run-in period, which is carried out by their investigator. Until now In HDP research there are no factors known to predict the outcome. The following factors are assessed at baseline: age, sex, education (medical student or doctor), history of former chronic disease, former homeopathic treatment, former participation in a homeopathic drug proving. Subjects and investigators are also asked to rate their expectations about the subjects' responsiveness to homeopathic drugs as ordinals with 4 levels, as the authors presume that this could be a factor related to the outcome.

#### Questions to subject

A. "How would you estimate your sensitivity to homeopathic remedies in general?" - possible answers: strong reaction/reaction/slight reaction/no reaction; B. "How do you expect to react to the homeopathic drug?" - answers: a very high number of symptoms/many symptoms/low number of symptoms/no symptoms.

#### Questions to investigators

A "How would you estimate your subject's sensitivity to homeopathic remedies in general?" - Response options: same as above; B: "What is your expectation about your subjects reaction to the homeopathic drug?" - response options same as above.

After starting the trial, subjects are required to document daily any new or uncommon symptoms in a semi-structured trial diary accessed through a secure internet connection. It will provide a head-to-feet structure to be filled in with free text. Every third day each subject will be contacted by phone by his or her investigator. This optimises the homeopathic quality of documentation, which is considered crucial for a successful HDT [16]. A very detailed description of symptoms experienced by the subjects is essential for the quality of the homeopathic drug proving trial. Of special importance are precise descriptions of locations, sensations, modalities, concomitant symptoms, changes in mental or emotional state. Any strange, individual, uncommon and peculiar symptoms observed should be documented as these are considered most important for the homeopathic purpose. Investigators are only permitted to read and separately comment on the documentation of their subjects. The purpose of the supervision by the investigators and the additional documentation is to highlight special symptoms, improve documentation or mark special observations as is common in HDP. Investigators are not able to change the documentation of their subjects. Their documentation is saved and stored separately.

